##### Education

Awareness-raising of the importance of fruit and vegetables to healthy eating and health in general, as well as the range of low-cost fruits and vegetables available and the relative costs compared with other foods. In-season produce will also be identified. This component is aimed at increasing the proposed theoretical mediators, perceived knowledge and value of increased fruit and vegetable consumption and perceived affordability of fruits and vegetables.

##### Skill-building

To foster behavioural skills in budgeting; meal planning; and meal preparation strategies including provision of shopping lists linked to simple recipes. This is aimed at increasing the theoretical mediators, self-efficacy and perceived affordability.

##### Goal-setting

This is a key behaviour change activity identified as a common element of successful previous fruit/vegetable interventions. For example, women will be encouraged to increase their and their families' vegetable consumption to meet the Australian recommendation of five 75 gram serves/day.

##### Overcoming barriers

Tips will be provided on overcoming commonly-reported barriers to increased fruit and vegetable consumption identified from our previous work. For example, suggestions will be provided on engaging familial involvement/support, given theoretical arguments and previous literature on the importance of social influences on behaviour. This component targets the theoretical mediator of perceived barriers. In addition, the newsletters and online forum will be tailored according to whether or not women have young children living with them, since the presence of young children (under age 12) has been associated with particular barriers to healthy eating behaviours [34].

##### Social support

Access to the online forum will enable women to share ideas and support each other, as well as benefit from the reinforcement of messages provided in the newsletters. The forum will contain discussion boards with threads that coincide with the newsletter education and skill-building content. An Accredited Practicing Dietitian will answer any questions and add posts regularly to prompt discussion. For women with children, newsletters will include tips on garnering children's support/engagement in the healthy eating behaviour change processes.

A summary of the newsletter content, including the target mediators, the corresponding newsletter communication objectives, and the barriers and enablers targeted in each newsletter, are shown in Table 1.

**Table 1 T1:** Summary of skill-building intervention newsletter objectives, targeted mediators and content

**Newsletter Week (no)**.	Objective/target	Primary communication objective	Secondary objective (barriers and promoters addressed)
1(1)	Knowledge	Why you should eat more fruit and vegetables and drink water	- Health benefits - How much to eat/drink - Set goals to increase amount of vegetables

2(2)	Self-efficacy for healthy eating, perceived affordability of fruit & vegetables	Planning for healthy eating	- Planning a menu (inventory of items on hand) and writing a shopping list - Planning to drink more water

3(3)	Self-efficacy for healthy eating	Shop smart	- Saving money at the supermarket (using canned or frozen when fruit & vegetables not in season) - Understanding labels - Setting goals (related to buying more fruit & veg while shopping)

4(4)	Perceived affordability of fruit & vegetables, self-efficacy for healthy eating	Confidence in the kitchen	- Creating quick simple meals from items on hand (include cooking methods, adding fruit & vegetables to simple meals) - Preventing wastage - Fruit juice and sugar

5(5)	Perceived barriers	Saving time and money	- Meal ideas for saving time - Food safety (to avoid waste) - Soft drinks and sugar

7(6)	Perceived barriers	Trying different fruit & vegetables	- Tasting new/different fruit & veg - Healthy eating outside the home - Trying sweet-drink alternatives

9(7)	Self-efficacy for healthy eating, perceived barriers	Confidence in eating healthy at all times	- Modifying recipes - Eating fruit & vegetables in social situations - Energy deficit when reducing consumption of sweetened drinks

11(8)	Self-efficacy for healthy eating, perceived barriers, awareness	Revision	- Resources to use for continuing to eat healthy - Revision of key messages

Two sets of newsletters were created, tailored to women with, and to women without children aged 12 years or younger. All versions have been pilot tested in a sample of women from a range of socioeconomic backgrounds, and were modified on the basis of pilot feedback on the formatting, content and language (for example, in response to repeated requests for more recipes, the number of recipes accompanying newsletters was doubled).

#### Price reduction intervention

Participants in this intervention arm will receive price discounts equivalent to 20%, which will be applied electronically at the supermarket checkout on all healthier options (all fruits and vegetables, including fresh, tinned and frozen, and diet- or low-calorie soft drinks or water) purchased by study participants. A reduction of this magnitude is considered appropriate, since it is unlikely to lead to the unintended consequence of promoting additional snack food items that a larger price reduction might encourage [12]. The focus on low-joule soft drinks is justified from an energy-balance/obesity prevention perspective, as a substitute for their more commonly-consumed, high-joule sugar-sweetened versions, which is consistent with the Dietary Guidelines for Australian Adults [35]. Discounts will be linked to participants' store loyalty (Fly-Buys) cards, to ensure they receive a discount upon swiping their card at checkout. Participants will be provided with a list of all items for which price reductions apply at the start of the intervention, and a reminder list mid-intervention.

#### Skill-building and price reduction intervention

The combined group will receive (concurrently) both the skill-building and price reduction interventions detailed above.

#### Control group

Participants in the control group will complete the assessments only, until the intervention and six-month follow-up are complete, at which point they will be offered all print-based skill building intervention materials. Like the intervention participants, they will receive shopping vouchers and loyalty card points as compensation for their time and commitment (to the value of $75.00).

### Outcome assessments

Data will be collected pre- and immediately post intervention and at six-month follow up using a self-report questionnaire designed for the study which uses a combination of adapted previously validated measures and measures designed for the current study. The collection time-points for each measure are detailed in Table 2 below.

**Table 2 T2:** Summary of study measures

Measures	Baseline	Post-intervention	Follow-up
Outcomes			
Vegetable purchasing and consumption	✓	✓	✓
Fruit purchasing and consumption	✓	✓	✓
Water purchasing and consumption	✓	✓	✓
Sugar sweetened beverage purchasing and consumption	✓	✓	✓
Shopping habits (location, frequency)	✓	✓	✓
Mediators			
Food security	✓	✓	✓
Self-efficacy for planning, shopping, preparing and eating fruit and vegetables	✓	✓	✓
Self-efficacy for drinking water and reducing sugar sweetened beverages	✓	✓	✓
Perceived affordability of fruit and vegetables	✓	✓	✓
Convenience	✓	✓	✓
Personal and household preferences	✓	✓	✓
Demographic and other covariates			
Age	✓	✓	✓
Height	✓	✓	✓
Weight	✓	✓	✓
Country of birth	✓	-	-
Relationship status	✓	-	-
Healthcare card holder	✓	-	-
Household composition	✓	-	-
Income (individual & household)	✓	-	-
Educational qualifications	✓	-	-
Employment status	✓	-	-
Whether currently pregnant	✓	✓	✓
Whether currently dieting	✓	✓	✓
Vegetarian status	✓	-	-
Smoking status	✓	-	-
Economic evaluation questions	✓	✓	✓
Process evaluation questions	-	✓	✓

#### Primary outcome measures

Purchasing and consumption of fruits, vegetables, and sugar-sweetened high-joule soft (carbonated) drinks vs. low-joule (carbonated) soft drinks/water are the primary outcomes. Data on purchasing of fruits, vegetables, high-joule sugar-sweetened soft drinks, low-joule soft drinks and water, and total grocery shopping purchases, will be gathered using electronic sales data, which Coles will provide for consenting participants via their store loyalty cards (Fly-Buys).

Fruit and vegetable consumption will be assessed using a series of self-reported food frequency questions adapted from the 1995 National Nutrition Survey which has been previously validated against food record data [36]. Measures of daily equivalent fruit and vegetable purchasing quantities (adjusted for household members/composition) and daily equivalent serves consumed will be calculated.

Sugar-sweetened high-joule beverage consumption, and low-joule beverage and water consumption will also be measured using a modified version of the previously validated measure [37] which asks respondents to record how much serves of each beverage they usually drink each day.

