This paper describes the protocol for the Supermarket Healthy Eating for Life (SHELf) study, a randomised controlled trial that will build on an important intersectoral partnership with Coles Supermarkets, a major national supermarket chain, and the National Heart Foundation of Australia. Supermarkets are a major controller of food access, pricing and affordability [23]. Supermarkets and grocery stores accounted for 64% ($75 billion) of the total food retail in Australia in 2007-8 [23]. Coles Supermarkets are the second-largest grocery chain in Australia, with around 740 stores nationally. Coles Supermarkets have a store loyalty program called FlyBuys. Shoppers who sign up to FlyBuys are given a credit card style membership card which can be scanned every time a purchase above five Australian dollars is made at a participating FlyBuys business. This allows members to collect points which can then be exchanged for rewards. The National Heart Foundation of Australia is a not-for-profit non-government organization whose mission is to reduce suffering and death from heart, stroke and blood vessel disease in Australia, with nutrition promotion a key focus.

SHELf aims to address the gaps in the existing literature identified above. It tests the effectiveness and cost-effectiveness of a skill-building intervention, a price reduction intervention, and a combined skill-building and price reduction intervention, against a control condition, in promoting purchasing of fruits and vegetables, reducing purchasing of sugar-sweetened soft drinks, and increasing purchasing of low-joule soft drinks/water amongst women (of both high and low socioeconomic status). Secondary aims are to test the impact of the intervention on increasing self-efficacy for, and perceived affordability of, healthy eating, and to examine the contribution of self-efficacy and perceived affordability as mediators of changes in purchasing and consumption behaviours resulting from the intervention. The SHELf study will build upon and extend the SHOP study by drawing on two theoretical frameworks (Social Ecology Theory [24] and Social Cognitive Theory [25]), and by incorporating a skills-based intervention component (rather than education alone), utilizing strategies shown to be feasible and effective in the Australian context in the Food Cent$ study.

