#### Economic evaluation

A cost-consequences analysis will be conducted from a societal perspective comparing incremental costs and outcomes in each of the three intervention arms to the control arm. Main resource use data will be collected during the trial and follow-up period via surveys at baseline, pre- and post-intervention, project team records and Coles electronic sales data, supported by interviews with the project team. Household cost impact will be determined through external (Coles) data on food purchasing combined with individual self-report data on non-Coles and Coles-non-Flybuys food purchasing over the course of the intervention and follow-up period. Participant time and related travel expenses will be estimated from self-report data via study questionnaires. Sensitivity analyses will be conducted on key cost and outcome data. Given the short time-frame of the intervention and the follow-up period (less than one year), no discount factor will be applied to costs and outcomes in the analyses.

Economic evaluation results will give rigorous evidence to assist policy makers to make appropriate decision on resource allocation to such nutrition interventions at population level and to determine the cost-effectiveness of nationwide roll-out.

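### In the two discount arms the card swipe that earns the 20% discount also records purchasing, so carded purchases of discounted items can rise without more being bought

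*Protocol article*

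**What the plan says.** Under Primary outcome measures, the protocol article states: "Purchasing and consumption of fruits, vegetables, and sugar-sweetened high-joule soft (carbonated) drinks vs. low-joule (carbonated) soft drinks/water are the primary outcomes". The purchasing part "will be gathered using electronic sales data, which Coles will provide for consenting participants via their store loyalty cards (Fly-Buys"). The only adjustment described there is for household size and make-up: "Measures of daily equivalent fruit and vegetable purchasing quantities (adjusted for household members/composition) and daily equivalent serves consumed will be calculated".

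The Price reduction intervention section says: "Participants in this intervention arm will receive price discounts equivalent to 20" per cent on fruit, vegetables, low-joule soft drinks and water. On delivery it says: "Discounts will be linked to participants' store loyalty (Fly-Buys) cards, to ensure they receive a discount upon swiping their card at checkout". The discount also applies in a second arm: "The combined group will receive (concurrently) both the skill-building and price reduction interventions detailed above".

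The plan expects some purchases to fall outside the card record. For household cost, the Economic evaluation section uses sales data "combined with individual self-report data on non-Coles and Coles-non-Flybuys food purchasing over the course of the intervention and follow-up period". The Background notes that the card "can be scanned every time a purchase above five Australian dollars is made at a participating FlyBuys business", so very small purchases may go unrecorded in every arm. Table 2 collects shopping location and frequency at all three waves, and the Mediator measures section treats shopping practices as potential mediators. The Data analysis section names confounders for the GEE models, but none concerns the share of shopping that the card captures.

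**The concern.** The device that records the outcome is the device that pays the intervention. A woman in a discount arm gains 20% on the target foods each time she swipes, and gains again if she buys at Coles what she used to buy elsewhere. A woman in the control or skill-building arm has only ordinary loyalty points. The recorded share of true purchasing can therefore change after randomisation in two arms and not in the others.

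There is room for such a change. A regular shopper may visit as seldom as about once a fortnight (Participant identification). Continued card use rests on stated willingness (Eligibility criteria). Intention-to-treat analysis, GEE and baseline adjustment deal with stable differences between women. They do not deal with a change in capture that the discount itself sets off.

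At stake is how the price and combined arms compare with control, and with skill-building, on purchasing. Purchasing leads the stated aim and is the outcome named in the sample-size section. The Discussion says the results may support fiscal policy, for which moving purchases between shops and buying more are very different findings.

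**Working it through.** **Inputs from the Sample Size section.** Target difference 0.5 serves/day; mean vegetable intake 1.9 serves/day in women of low socioeconomic position and 1.9 + 0.5 = 2.4 in those of higher position; SD 1.1; z-values 1.96 and 0.84.

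**The plan's own figure.** 2 × 1.1² × (1.96 + 0.84)² / 0.5² = 75.9, so 76 per group and 304 in total. 304 / 0.70 × 1.1 = 477.7, so 478. Both reproduce, and the sample-size arithmetic is not in question here.

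**Spurious difference.** Let T be true daily purchasing, equal in both arms, and let c1 and c0 be the shares captured on the card in a discount arm and a comparison arm. Recorded purchasing is T × c, so the recorded difference is T × (c1 − c0) although the true difference is zero.

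**Chance of a significant result favouring the discount arm.** With 76 per arm, SE = 1.1 × √(2/76) = 0.178, and the chance is Φ(difference / SE − 1.96). The nominal rate in that direction is 2.5%.

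| Rise in capture | Difference, T = 1.9 | Chance | Difference, T = 2.4 | Chance |
|---|---|---|---|---|
| 5 points | 0.095 | 8% | 0.12 | 10% |
| 10 points | 0.19 | 19% | 0.24 | 27% |
| 15 points | 0.285 | 36% | 0.36 | 52% |
| 20 points | 0.38 | 57% | 0.48 | 77% |
| 25 points | 0.475 | 76% | 0.60 | 92% |

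A 10-point rise gives 0.19/0.5 = 38% to 0.24/0.5 = 48% of the target. The whole target is reached at 0.5/1.9 = 26 points or 0.5/2.4 = 21 points. With all 125 per arm analysed, a 20-point rise at T = 1.9 gives 78%.

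**A check without the intake figures.** If capture starts at 50% to 80% (assumed), a 10-point rise lifts recorded purchasing by 0.10/0.80 = 12.5% to 0.10/0.50 = 20%.

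**What is assumed.** The documents give no capture share, so the range of 5 to 25 points is mine. The means and SD are self-reported consumption and stand in for household-adjusted sales, whose spread is unknown. The test is a simple comparison of two means, not the planned GEE model of change. The table shows how sensitive the comparison is to capture. It does not forecast the trial's error rate.

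**The case against.** The best reply is that the plan already collects much of what is needed. Consumption is also a primary outcome and does not depend on the swipe. Total grocery purchases come with the sales data. Shopping location and frequency are asked at every wave, and shopping practices are measured as potential mediators, so a change of shop by arm could be seen. How these enter a sensitivity analysis might be left to a fuller document.

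Much of this stands, and it limits the point. It does not remove it. The article states the source of the purchasing outcome and assigns the off-card data to household cost. Those data are described as food purchasing in general, with no statement that fruit, vegetable and drink quantities are asked separately. If they are not asked, no later analysis plan can recover them. Treating shopping practices as mediators could even lead a change of shop to be read as a mechanism of benefit.

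A reader might also infer that every purchasing result in the discount arms is biased towards benefit. The documents do not support that:

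- Sugar-sweetened drinks are not discounted. Greater capture would record more of them and bias against benefit.
- The incentive runs for the three-month intervention and may fade by the six-month follow-up.
- Skill-building versus control carries no discount-driven bias.
- Nothing in the documents shows that a shift will occur, or how large it would be.

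**Conclusion.** The point holds in limited form. As written, the plan can record a rise in purchasing of discounted items in the price and combined arms, relative to control or skill-building, when total purchasing has not risen. The risk lies mainly in the discount period. The conclusion needs only that the same swipe pays the discount and records the outcome, and that the stated outcome and model contain no correction for capture. Both can be read directly from the article.

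The size is unknown. The illustrative range runs from a minor distortion at 5 points to the full 0.5-serve target at 21 to 26 points. It would be wrong to conclude that the purchasing results are certain to be false, or that the rejection rates above are those of the planned analysis.

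**What to change.** Keep carded sales as the objective purchasing measure, and add the following.

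1. **Sensitivity analysis.** Pre-specify an analysis of total purchasing, defined as carded Coles quantity plus self-reported non-Coles and Coles-without-card quantity. Ask the self-reported part separately for fruit, vegetables and drinks at each wave.
2. **Capture checks by arm.** Report carded shopping days, total carded grocery spend and shopping location at each wave.
3. **Rule for interpretation.** State in advance that a carded increase in a discount arm will not be read as increased purchasing unless these checks and the co-primary consumption outcome are consistent with it.

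The cost is a few more items in a questionnaire that already runs at three waves, plus analysis wording. The self-reported part is noisy. Because participants are not blinded, its error may itself differ by arm. For that reason it belongs in a sensitivity analysis and should not replace the sales measure.

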#### Mediator measures

Perceived barriers to fruit and vegetable consumption such as taste, availability, cost, quality, food waste, and knowledge about food preparation and meal planning will be assessed as potential mediators using items adapted from previously published scales [38-40]. Self-efficacy regarding reducing the consumption of sugar-sweetened high-joule beverages and increasing the consumption of water, and cooking skills will be measured using questions adapted from previously published measures [39,41]. Shopping practices and price considerations will also be measured as potential mediators using questions adapted from two previously published studies [22,42].

#### Demographics and other covariates

Demographic characteristics and other covariates will be assessed by questions on constructs as shown in Table 2, using standard measures.

#### Economic evaluation

A cost-consequences analysis will be conducted from a societal perspective comparing incremental costs and outcomes in each of the three intervention arms to the control arm. Main resource use data will be collected during the trial and follow-up period via surveys at baseline, pre- and post-intervention, project team records and Coles electronic sales data, supported by interviews with the project team. Household cost impact will be determined through external (Coles) data on food purchasing combined with individual self-report data on non-Coles and Coles-non-Flybuys food purchasing over the course of the intervention and follow-up period. Participant time and related travel expenses will be estimated from self-report data via study questionnaires. Sensitivity analyses will be conducted on key cost and outcome data. Given the short time-frame of the intervention and the follow-up period (less than one year), no discount factor will be applied to costs and outcomes in the analyses.

Economic evaluation results will give rigorous evidence to assist policy makers to make appropriate decision on resource allocation to such nutrition interventions at population level and to determine the cost-effectiveness of nationwide roll-out.

#### Process evaluation

Participants will be asked in the post-intervention and follow-up assessment to provide subjective evaluations of the usefulness of materials given and the discounts offered.

### Data analysis

Outcomes will be analysed on an intent-to-treat basis. Generalized Estimating Equations [43] will be used to fit regression models to describe the effects of the intervention on outcome and mediator variables. Generalized Estimating Equations represents an extension of the General Linear Model that allows parameter estimation for correlated data (e.g., from repeated measurements of participants). Models will be fitted to determine differences in changes in the outcome and mediator variables in the intervention and control groups. Potential confounders (e.g., age, education, country of birth, relationship status, employment status, household income, household composition) will be controlled for as necessary. Mediation analyses will be undertaken using the MacKinnon method [32]. Descriptive statistics (for quantitative data), content and thematic analysis (for qualitative data) will be used as appropriate to analyse the process evaluation data. StataSE v.11.2 [44] will be used for all statistical analyses.

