#### Sample Size

Sample size calculations are based on the ability to detect increases in fruit and vegetable purchasing of at least 0.5 serves per day (in Australia, a standard serve is equivalent to 75 grams vegetables or 150 grams fruit). There is evidence that this increase is feasible; for example, a review of the literature on fruit and vegetable intervention studies [19] found an average increase of 0.6 serves of fruit/vegetables per day across studies. The Australian Go for 2&5 campaign achieved a population net increase of 0.8 in the mean number of servings of fruit and vegetables per day over three years [30]. Even small population increases in fruit and vegetable consumption are meaningful. For example, an increase of 80 g per day of fruit and vegetables has been estimated to reduce the risk of ischaemic heart disease by 10%, ischaemic stroke by 6%, lung cancer by 4% and oesophageal cancer by 6% [31].

Of the outcome variables (fruit and vegetable purchasing), it is estimated that the most challenging to shift will be vegetable purchasing, therefore we have based our sample estimates on this outcome. There are no recent national dietary survey data in Australia (with the last national survey of adults conducted in 1995), so we have based our estimates on more recent data collected in a large community-based survey of over 1500 women [5]. In that study, women of low socioeconomic position reported consuming on average 1.9 serves of vegetables per day (0.5 serves fewer than those of higher position), with a standard deviation of 1.1. Therefore, to detect an increase of 0.5 serves of vegetables, using the following formula to calculate the sample size for a continuous measure:

N per group = 2 * SD^2 ^* (Zsign + Zpower)^2 ^/delta^2 ^, where SD = 1.1; delta = 0.5; Zsign for 5% type 1 error is 1.96 and Zpower for 20% type 2 error is 0.84, N per group = 76, totalling 304. Inflating our estimate to adjust for attrition/loss to follow-up (conservatively estimated at around 10% at each measurement wave), and to account for potential design effects based on sampling within catchment areas (conservatively estimated at 1.1 or an inflation of 10%), our total minimum sample size is 304/0.70 * 1.1 = 478 (rounded up to 500, or 125 in each group).

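### The planned difference-in-change models are not stated to adjust for the baseline outcome, and the covariate set is left open; fixing both in advance costs nothing and protects the planned power

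*Protocol article*

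**What the plan says.** The Data analysis section of the protocol article specifies Generalized Estimating Equations and describes the target as follows: "Models will be fitted to determine differences in changes in the outcome and mediator variables in the intervention and control groups". It does not say how the baseline measurement enters the model, and no other section names the baseline value of the outcome as a covariate. On further adjustment it says: "Potential confounders (e.g., age, education, country of birth, relationship status, employment status, household income, household composition) will be controlled for as necessary". It gives no criterion for when adjustment is needed.

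One covariate is fixed elsewhere. The end of the Sample Size section says that catchment area will be controlled for; the Randomisation section stratifies by its socioeconomic status.

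The Sample Size section uses the two-sample formula for a continuous measure. Its SD comes from one cross-sectional survey of reported vegetable intake ("with a standard deviation of 1.1"). No correlation between repeated measurements appears.

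**The concern.** There are two linked weaknesses.

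First, the sizing and the analysis rest on different variances. The formula compares means measured once. A difference in change has a variance that depends on how strongly a woman's baseline and later values correlate. If that correlation is low, subtracting baseline adds noise and the trial has less power than planned. Using baseline as a covariate avoids this, and the data are already collected.

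Second, randomisation leaves no systematic confounding by baseline variables to detect, so a rule to control confounders when needed has nothing to act on. In practice the covariate set could be settled after seeing how estimates move. This matters more here because there are several primary outcomes, three comparisons with control and two assessment times.

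**Working it through.** **Inputs from the Sample Size section.** Two-sided 5% error ("Zsign for 5% type 1 error is 1.96"); 80% power ("Zpower for 20% type 2 error is 0.84"); delta 0.5 ("to detect an increase of 0.5 serves of vegetables"); SD 1.1. **Assumption:** the correlation rho between baseline and one later measurement is not in the document, so a range of 0.2 to 0.8 is shown, with the same SD at both times.

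**1. Reproduce the plan's figure.** n per arm = 2 × 1.1² × (1.96 + 0.84)² / 0.5² = 2 × 1.21 × 7.84 / 0.25 = 75.9, that is 76. Then 4 × 76 = 304, and 304 / 0.70 × 1.1 = 477.7, that is 478. This matches "N per group = 76, totalling 304" and the total given. Power at 76 per arm with SD 1.1 is 80.0%.

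**2. Variance per woman under each analysis.**
- Single later measurement (as sized): SD².
- Change from baseline: 2(1 − rho) × SD².
- Adjusted for baseline: (1 − rho²) × SD².

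Change minus adjusted is (1 − rho)² × SD², which is never negative. The ratio is 2/(1 + rho): 1.54 at rho 0.3 and 1.25 at rho 0.6.

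**3. Power.** Power = Φ(0.5 / (s × √(2/n)) − 1.96), where s is the square root of the variance above. Example at rho 0.3, n = 76:
- Change: s = 1.1 × √1.4 = 1.302; standard error 0.211; 0.5/0.211 − 1.96 ≈ 0.41; power 66%.
- Adjusted: s = 1.1 × √0.91 = 1.049; standard error 0.170; 0.5/0.170 − 1.96 ≈ 0.98; power 84%.

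| rho (assumed) | Power, change | Power, adjusted | n per arm for 80%, change | n per arm for 80%, adjusted |
|---|---|---|---|---|
| 0.2 | 60% | 82% | 122 | 73 |
| 0.3 | 66% | 84% | 107 | 70 |
| 0.4 | 73% | 86% | 92 | 64 |
| 0.5 | 80% | 90% | 76 | 57 |
| 0.6 | 88% | 94% | 61 | 49 |
| 0.7 | 95% | 98% | 46 | 39 |
| 0.8 | 99% | 99.7% | 31 | 28 |

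**4. Where the change analysis drops below 80%.** At n = 76 this happens when 2(1 − rho) exceeds 1, so rho below 0.5. With 125 recruited per arm and the plan's design effect of 1.1:
- 30% lost: 125 × 0.70 / 1.1 = 79.5 effective; threshold rho about 0.48.
- 20% lost: 125 × 0.80 / 1.1 = 90.9; threshold about 0.40.
- 10% lost: 125 × 0.90 / 1.1 = 102.3; threshold about 0.33.

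**5. Size of the covariate freedom.** The seven named examples, each in or out, give 2⁷ = 128 possible sets, and the list is introduced as examples only.

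**The case against.** The strongest reply is that an article condenses the plan. Its one sentence on change describes what is estimated and does not fix the parameterisation. A model that constrains baseline means to be equal across arms, with a suitable working correlation, would already be efficient. This stands, and it is why the power figures are conditional on a group-by-time change analysis. It does not remove the point, because the sizing ignores correlation and nothing in the text commits the analysis to using baseline efficiently.

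A reader might also draw stronger conclusions that the document does not support:
- *That the analysis is unadjusted.* Catchment area is fixed as a covariate, and further adjustment is foreseen. What is absent is a stated adjustment for the baseline outcome.
- *That the trial is underpowered.* This depends on an unstated rho. At 0.6 or above the change analysis exceeds 80%, and with only 10% lost it does so above about 0.33.
- *That discretionary covariates lower power.* They do not. Any loss comes from change scores at low rho; the covariate rule is a separate issue of pre-specification.
- *That post-randomisation variables will be adjusted for.* Table 2 lists weight, pregnancy and dieting status ("Whether currently dieting") among covariates at all three waves, but it is a measurement schedule, and it repeats age and height too. Of the seven examples in Data analysis, six are collected at baseline only, and the intervention cannot affect age. Later values are not excluded, but no section says they enter the effect model.
- *That GEE will be biased by dropout.* This would require an assumed working correlation and dropout mechanism, neither of which is stated.

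The Blinding section keeps the chief investigators and the data manager, who prepare and analyse the data, blind to arm. That limits steering towards a favoured arm. It does not fix the model, since estimates for coded arms can still be seen to move with each choice.

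**Conclusion.** The point holds as an avoidable weakness, not an error that invalidates the trial. If the model is a change analysis, its variance is 1.25 to 1.54 times that of the baseline-adjusted analysis for rho between 0.6 and 0.3. The direction does not depend on rho; the size does. Whether power falls below the planned 80% depends on rho being under about 0.5 at 76 per arm, or under 0.33 to 0.48 for losses of 10% to 30% from 125 per arm. Baseline adjustment keeps power above 80% across the range examined. These figures are for one post-baseline time point, with the plan's delta and SD taken as given.

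The open covariate rule is a lesser matter. It is partly detail that an analysis plan could supply and is softened by blinding, but as worded it has no confounding rationale and sets no limit on choice after the data are seen.

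**What to change.** Replace the sentence on confounders with a fixed specification:
- Every primary model includes the baseline value of the same outcome and catchment area. Alternatively, baseline means are constrained equal across arms, with a stated working correlation other than independence, because the gain in that form comes from modelling the correlation.
- A short list of further covariates is named in advance and is the same for all arms and time points. The Primary outcome measures section already adjusts purchasing quantities for household composition, so the list should say whether that variable is entered again for purchasing outcomes.
- Only baseline-measured values are used; any other adjustment is reported as a sensitivity analysis.
- The assumed rho is stated beside the sample size.

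The cost is wording only. Table 2 schedules the outcomes and the named covariates at baseline, and sample size, visits and data collection do not change.
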